### Secondary outcomes

The secondary outcomes encompass several measures, including the need for airway maneuvers, blood pressure changes, sleep quality assessment, pro-inflammatory cytokine levels, and monitoring of adverse events such as bradycardia, tachycardia, nausea, and vomiting.

For this study, airway maneuvers will be defined as jaw-lift, positive-pressure ventilation with a bag-mask, insertion of a laryngeal mask, or endotracheal intubation.

Blood pressure will be measured at different time points: before IMT, prior to anesthesia, during the examination, and in the PACU.

Sleep quality and duration will be assessed using the Pittsburgh Sleep Quality Index (PSQI), a 19-item questionnaire (Table 3), at T1, T2, T4, T5, and T6. A patient scoring greater than 5 on the PSQI will be classified as a poor sleeper (35).

**Table 3 tab3:** The questionnaire of Pittsburgh Sleep Quality Index.

1. During the past month, when have you usually gone to bed?				
2. During the past month, how long (in minutes) has it taken you to fall asleep each night?	≤15 min (0)	16 ~ 30 min (1)	31 ~ 60 min (2)	>60 min (3)
3. During the past month, when have you usually gotten up in the morning?				
4. During the past month, how many hours of actual sleep did you get that night? (This may be different than the number of hours you spend in bed)	>7 h (0)	6 ~ 7 h (1)	5 ~ 6 h (2)	<5 h (3)
5. During the past month, how often have you had trouble sleeping because you…	Not during the past month (0)	Less than once a week (1)	Once or twice a week (2)	Three or more times a week (3)
a. Cannot get to sleep within 30 min	(0)	(1)	(2)	(3)
b. Wake up in the middle of the night or early morning	(0)	(1)	(2)	(3)
c. Have to get up to use the bathroom	(0)	(1)	(2)	(3)
d. Cannot breathe comfortably	(0)	(1)	(2)	(3)
e. Cough or snore loudly	(0)	(1)	(2)	(3)
f. Feel too cold	(0)	(1)	(2)	(3)
g. Feel too hot	(0)	(1)	(2)	(3)
h. Have bad dreams	(0)	(1)	(2)	(3)
i. Have pain	(0)	(1)	(2)	(3)
j. Other reason(s), please describe, including how often you have had trouble sleeping because of this reason(s)	(0)	(1)	(2)	(3)
6. During the past month, how often have you taken medicine (prescribed or “over the counter”) to help you sleep?	Not during the past month (0)	Less than once a week (1)	Once or twice a week (2)	Three or more times a week (3)

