7. During the past month, how often have you had trouble staying awake while driving, eating meals, or engaging in social activity?	Not during the past month (0)	Less than once a week (1)	Once or twice a week (2)	Three or more times a week (3)
8. During the past month, how much of a problem has it been for you to keep up enthusiasm to get things done?	Not during the past month (0)	Less than once a week (1)	Once or twice a week (2)	Three or more times a week (3)
9. During the past month, how would you rate your sleep quality overall?	Very good (0)	Fairly good (1)	Fairly bad (2)	Very bad (3)

Component		Componen*t* score
Sleep quality	#9 Score	
Time to fall asleep	#2 Score + #5a Score (0 = 0; 1 ~ 2 = 1; 3 ~ 4 = 2; 5 ~ 6 = 3)	
Bed time	#4 Score	
Sleep efficiency	#4/(#3 – #1) * 100% (>85% = 0, 75–84% = 1, 65–74% = 2, <65% = 3)	
Somnipathy	# sum of scores 5b to 5j (0 = 0; 1 ~ 9 = 1; 10 ~ 18 = 2; 19 ~ 27 = 3)	
Hypnotics	#6 Score	
Daytime dysfunction	#7 score + #8 score (0 = 0; 1 ~ 2 = 1; 3 ~ 4 = 2; 5 ~ 6 = 3)	

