**Score of Pittsburgh Sleep Quality Index**		

This scale is designed to record your own assessment of any sleep difficulty you might have experienced. Please complete this scale at T1, T2, T4, T5, and T6. All scales will be finally e-mailed to designated anesthesiologist. (T1: one day before inspiratory muscle training, T2: the moment before anesthesia, T4: the night of gastroscopy, T5: 1 week after gastroscopy, T6: 4 weeks after gastroscopy).

At three different time points, namely T1, T2, and T3, 5 mL of venous blood will be collected from the patient’s elbow. The collected blood samples will be processed through conventional centrifugation to separate the plasma. Subsequently, radioimmunoassay will be employed to measure the plasma levels of pro-inflammatory cytokines, including tumor necrosis factor-alpha (TNF-α) and interleukin-6 (IL-6).

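### The PSQI recalls the past month but is also given on the night of gastroscopy and one week later, so neither T4 nor T5 can isolate sleep after the procedure

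*Protocol article*

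**What the plan says.** Protocol article, Secondary outcomes: sleep quality and duration are measured with the PSQI, "a 19-item questionnaire (Table 3), at T1, T2, T4, T5, and T6", and a total above 5 classes the patient as a poor sleeper.

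Table 3 prints the form. All nine numbered items open with a past-month recall, from the first ("During the past month, when have you usually gone to bed") to the last ("During the past month, how would you rate your sleep quality overall"). The stem of item 5 carries the same recall for 5a to 5j. Item 4 mixes two periods: "During the past month, how many hours of actual sleep did you get that night".

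The note under Table 3 applies this one form throughout: "Please complete this scale at T1, T2, T4, T5, and T6". It dates the last three as "T4: the night of gastroscopy, T5: 1 week after gastroscopy, T6: 4 weeks after gastroscopy". T2 is placed directly before anesthesia, so T2 and T4 share a calendar day. No version with a shorter recall is given.

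The scoring key in Table 3 sets the sleep-efficiency bands as ">85% = 0, 75–84% = 1, 65–74% = 2, <65% = 3". Item 4 scores 6 to 7 h as 1 and 5 to 6 h as 2.

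**The concern.** The schedule has three sleep assessments after the procedure, and the Strengths section names procedural sedation as a possible harm to sleep. T4 and T5 look designed to follow sleep in the first night and first week after sedation. A form that looks back a month cannot do that so soon. Most of what it records at T4 and T5 is the 4-week training period that T2 already covers. A level course from T2 through T4 to T5 would then say little about whether sleep was disturbed after the gastroscopy.

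Item 4 adds ambiguity. At T4 some patients may report one night and others a typical night of the month.

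The scoring bands are a separate matter. Where an answer fits two bands or none, somebody has to choose the component score, and the poor-sleeper classification depends on the sum.

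**Working it through.** The documents state no figure for this point, so there is none to reproduce. The check compares each recall window with the date of the procedure.

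**Inputs**
- Nights after the procedure, from the time-point definitions in the Intervention section and under Table 3: T2 = 0; T4 = 0 if completed before sleeping, 1 if that night counts; T5 = 7; T6 = 28.
- Length of a month, M: assumed to be 28 to 31 nights, because the documents give no number of days.
- Training lasts 4 weeks (28 nights) before gastroscopy. The gastroscopy is assumed to follow directly.

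**Share of the window after the procedure** = nights after the procedure / M

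| Time point | Nights after | M = 28 | M = 30 | M = 31 |
|---|---|---|---|---|
| T2 | 0 | 0% | 0% | 0% |
| T4, before sleep | 0 | 0% | 0% | 0% |
| T4, that night counted | 1 | 3.6% | 3.3% | 3.2% |
| T5 | 7 | 25.0% | 23.3% | 22.6% |
| T6 | 28 | 100% | 93.3% | 90.3% |

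**Overlap of T4 with T2.** Both windows end on the same day. They share all M nights if T4 is completed before sleep, and M − 1 of M nights otherwise (27/28 = 96.4% to 30/31 = 96.8%).

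**Content of T5.** M − 7 = 21 to 24 nights precede the gastroscopy, which is 75.0% to 77.4% of the window. All of them lie within the 28 nights of training.

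**Duration bands.** An answer of exactly 6 h lies in both the 6 to 7 h band (score 1) and the 5 to 6 h band (score 2).

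**Efficiency bands** (hours asleep / hours in bed)
- 8.5/10 = 85.0%. This is not above 85 and not within 75 to 84, so it has no score.
- 5.5/6.5 = 84.6%. It has no score as it stands. Rounded to a whole percent it becomes 85%, which has none either.
- Values between 74% and 75% also have no score as printed, but whole-percent rounding would resolve them.

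**Effect at the cut.** Suppose the other six components sum to 4 and the patient sleeps 6 h. The total is 4 + 1 = 5 (not a poor sleeper) or 4 + 2 = 6 (poor sleeper), depending on the band chosen.

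**The case against.** A reader might infer that the T4 and T5 assessments carry no information. The documents do not support that. The randomized contrast is loaded against unloaded training, sedation follows the same strategy in both arms, and the Statistical analysis section lists two-sample types of test without naming a T2-to-T4 change. Since the T4 and T5 windows are mostly the training month, an arm difference there can still reflect sleep during training, which the Strengths section gives as a reason for measuring sleep. This part of the objection stands.

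A reader might also infer that a change after the procedure shrinks in proportion to the share of nights in the table above. That does not follow, because much of Table 3 scores ordinal frequency categories, not averages over nights. Take a patient with no trouble before the procedure and trouble on all 7 nights after it. Over 30 days that is 7/(30/7) = 1.6 times a week, which scores 2 of 3 on that item. If the procedure night counts at T4, one bad night is 1/(30/7) = 0.23 times a week and scores 1 instead of 0. The form can therefore respond. What it cannot do is separate the nights after the procedure from those before.

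Nor do the documents say that a level course from T2 to T5 will be reported as no effect of sedation on sleep. That is a risk of interpretation only.

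On the scoring, each slip is worth one point on one component and matters for the classification only when the total is near 5. The data collectors are blinded, so the likely result is noise and not bias between arms. The documents do not show how often such answers will occur.

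Which sleep contrast should be the main one is a matter for the analysis plan, which is not shown, and is no part of this point.

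**Conclusion.** The mismatch is real and stands in the printed form and schedule, so it is not something left to a fuller document. T4 is nearly redundant with T2: at most one night in 28 to 31 differs. T5 blends 21 to 24 nights of the training period with 7 nights after the procedure. Neither isolates sleep after the gastroscopy; of the post-procedure assessments only T6 has a window that is wholly or almost wholly post-procedure. T1 and T2 suit a one-month recall.

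The result rests on a month of 28 to 31 nights and on patients following the printed recall period. Item 4's mixed wording makes the second assumption less secure at T4.

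The double score at 6 h and the missing score at 85% efficiency are smaller, independent defects.

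The consequence is limited to one secondary outcome. The hypoxemia endpoint and the sample size are unaffected.

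**What to change.** 1. Keep the past-month PSQI at T1, T2 and T6.
2. At T4 and T5, drop the PSQI or replace it with a short sleep rating covering last night (T4) and the past week (T5). Do not score that rating as a PSQI or cut it at 5. If the T4 rating is meant to cover the procedure night, it has to be completed the next morning.
3. Reword item 4 so that it refers to one recall period only.
4. Make the bands exhaustive and exclusive: efficiency at least 85%, 75 to below 85%, 65 to below 75%, and below 65%; assign exactly 6 h to one duration category.

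The cost is a revision of Table 1, the Secondary outcomes text and the form. The trial gives up a PSQI total at T4 and T5. At T4 that loses almost nothing beyond T2; at T5 it loses a mixed score that could not be attributed to the week after the procedure.

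### PSQI item 4 in Table 3 names two recall windows at once, which exposes two of the seven components to avoidable noise

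*Protocol article*

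**What the plan says.** Sleep quality is one of the secondary outcomes. It is measured with the 19-item PSQI printed in Table 3 of the protocol article, and the patient instruction under that table reads "Please complete this scale at T1, T2, T4, T5, and T6".

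Item 4 asks "During the past month, how many hours of actual sleep did you get that night". The two items that fix time in bed are worded as habits: item 1 is "During the past month, when have you usually gone to bed" and item 3 is "During the past month, when have you usually gotten up in the morning".

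The component table uses item 4 twice. Its score is the whole of the component labelled bed time. Its hours, divided by the interval from item 1 to item 3, give sleep efficiency. The total is then dichotomised: "A patient scoring greater than 5 on the PSQI will be classified as a poor sleeper".

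The instruction defines two of the visits as "T2: the moment before anesthesia, T4: the night of gastroscopy". Nothing in the article says which window governs item 4.

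**The concern.** One sentence sets two recall periods, and the form does not record which one the patient used. No later analysis can therefore recover it.

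A one-night reading is most plausible where a particular night is salient. At T2 that is the night before the endoscopy. At T4 it is the procedure night. T2 matters most, because it is the first PSQI after the 4 weeks of training and its past-month window coincides with those weeks. An item 4 answer for one possibly atypical night would not describe the training period. A change from T1 on the two affected components would then partly reflect which night each answer referred to.

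This is a wording problem in one item. It would remain if the visit schedule or the hour bands were changed.

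**Working it through.** The plan gives no figure on this point to reproduce, so the check applies the printed scoring directly.

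**Inputs from Table 3**
- Duration score: more than 7 h = 0, 6 to 7 h = 1, 5 to 6 h = 2, under 5 h = 3.
- Efficiency = item 4 hours / (item 3 − item 1) × 100%. Above 85% = 0, 75–84% = 1, 65–74% = 2, below 65% = 3. I closed the small gaps between bands by starting them at 85, 75 and 65.
- Seven components of 0 to 3, so the total runs from 0 to 7 × 3 = 21. Poor sleeper: total above 5.

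**Assumptions, not in the documents**
- Usual time in bed 8 h (varied from 6 to 9 h below).
- Usual sleep 6.5 to 7.5 h.
- Single nights normally distributed around the usual value with SD 0.75 to 1.5 h.

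**Step 1: points exposed.** Duration (0–3) plus efficiency (0–3) gives 0 to 6 of 21 points.

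**Step 2: effect of the window, 8 h in bed**

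| Item 4 answer | Efficiency | Duration + efficiency |
|---|---|---|
| 7.5 h | 93.75% | 0 + 0 = 0 |
| 7 h | 87.5% | 1 + 0 = 1 |
| 6.5 h | 81.25% | 1 + 1 = 2 |
| 5.5 h | 68.75% | 2 + 2 = 4 |
| 5 h | 62.5% | 2 + 3 = 5 |
| 4.5 h | 56.25% | 3 + 3 = 6 |

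A patient who usually sleeps 7.5, 7 or 6.5 h but reports one night of 4.5 h moves up by 6, 5 or 4 points. One night of 5.5 h moves the same patients up by 4, 3 or 2.

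**Step 3: crossing the cut-off on this item alone.** With the other five components at 0, a total above 5 needs 3 + 3. Item 4 must therefore be below both 5 h and 65% of usual time in bed, that is, below min(5, 0.65 × time in bed):
- 6 h in bed: below 3.9 h
- 7 h in bed: below 4.55 h
- 7.5 h in bed: below 4.875 h
- 8 to 9 h in bed: below 5 h

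**Step 4: how often a single night does this, 8 h in bed.** P(night < 5 h) = Φ((5 − usual) / SD):
- Usual 7.5 h, SD 0.75 h: z = −3.33, about 0.04%
- Usual 7 h, SD 1.0 h: z = −2, about 2%
- Usual 6.5 h, SD 1.5 h: z = −1, about 16%

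These are proportions of one-night answers. If only a share q of patients reads the item that way, the proportion of all forms is q times these values. At q = 0.5, for example, it is about 0.02% to 8%. The documents give no basis for q.

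**The case against.** The strongest reply is that the habitual reading is the natural one. All nine numbered items open with the past month, item 2 speaks of each night, and no night is named to which item 4 could refer. The phrase may be a slip for *per night*. The article is also in English for a single-centre trial in Xiamen, and the form actually handed to patients is not shown. This stands as a limit on size, because it leaves the share of patients affected unknown. It does not remove the contradiction, since Table 3 is printed as the instrument, with its instruction to patients.

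A reader might infer more than the text supports, in four ways:
- *That two components become pure one-night scores.* Only duration does. Efficiency keeps a usual-month denominator, so it is a hybrid.
- *That patients would often cross the cut-off on this item alone.* Step 4 shows that this needs an unusually short night in most of the assumed range. Smaller shifts in patients already near the cut-off are the more realistic route.
- *That ratios above 100% distort the score.* They can arise, but anything above 85% scores 0.
- *That the comparison between arms is biased.* Both arms complete the same form at the same visits, and nothing in the document makes a one-night reading likelier in one arm.

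**Conclusion.** The contradiction is real and is visible in the current text. It exposes up to 6 of 21 PSQI points to an unintended recall window, and it gives sleep efficiency a numerator and denominator that may refer to different periods. The supportable consequence is non-differential noise in one secondary outcome and a less interpretable change from T1, chiefly at T2 and T4. The amount of noise cannot be stated, because it depends on how many patients answer for one night. Time in bed, usual sleep and night-to-night variation are also assumed here. The hypoxaemia outcome and the sample size do not depend on this item. This is a minor defect that is worth correcting because the correction is nearly free.

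**What to change.** Reword item 4 of Table 3 to ask for the usual hours of actual sleep per night over the past month, so that it matches its own opening and items 1 and 3. Check the form issued to patients for the same wording, and correct it if it does not ask for usual sleep.

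The cost is a few words on one item and one check of the patient form, with no added visits, patients or analyses. Recruitment was planned from September 2023, the month of publication, so some forms may already have been completed. If those carried the ambiguous wording, record which version each patient answered.

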**Score of Pittsburgh Sleep Quality Index**		

This scale is designed to record your own assessment of any sleep difficulty you might have experienced. Please complete this scale at T1, T2, T4, T5, and T6. All scales will be finally e-mailed to designated anesthesiologist. (T1: one day before inspiratory muscle training, T2: the moment before anesthesia, T4: the night of gastroscopy, T5: 1 week after gastroscopy, T6: 4 weeks after gastroscopy).

At three different time points, namely T1, T2, and T3, 5 mL of venous blood will be collected from the patient’s elbow. The collected blood samples will be processed through conventional centrifugation to separate the plasma. Subsequently, radioimmunoassay will be employed to measure the plasma levels of pro-inflammatory cytokines, including tumor necrosis factor-alpha (TNF-α) and interleukin-6 (IL-6).

### Data collection, handling, and monitoring

We will gather the following data for this study:

Demographic data, including age, gender, and ASA physical status classifications.Physical examination data, including HR, mean arterial pressure (MAP), SpO_2_, respiratory rate, end-tidal carbon dioxide levels, Pi(max), BMI, neck circumference, and waist-hip ratio.Data related to the primary and secondary outcomes as mentioned earlier.Requirement for vasoactive agents, such as atropine, esmolol, phenylephrine, and urapidil hydrochloride.Need for rescue sedatives.

In order to prevent any loss of follow-up, a research assistant who knows the group assignment will reach out to patients from time to time. Their purpose is to remind patients to fill out the PSQI sheets.

To ensure data integrity and security, an independent monitor will oversee the data collection process. Data collectors will enter all raw data into Excel spreadsheets, which will then be stored in a separate database with restricted access using passwords. Additionally, original data and images will be securely stored on the research center’s computer, accessible only with login passwords. Unauthorized access to the database or computer will be strictly prohibited without the monitor’s permission.

In case of any adverse events, immediate attention will be given, followed by detailed recording and continuous follow-up. The Ethics Committee will periodically review the project’s progress and decide whether it should be continued.

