## Methods and analysis

### Study design

This study is a single-center, double-blinded RCT scheduled to take place at the Endoscopy Center of the First Affiliated Hospital of Xiamen University. Participants will be assigned randomly to either the intervention or control group in a 1:1 ratio. The protocol adheres to the Standard Protocol Items: Recommendations for Interventional Trials guidelines (33) and will be conducted following the study’s flow chart (Figure 1).

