### Intervention

This study aims to assess the impact of IMT on enhancing oxygenation levels during painless gastroscopy in individuals with a BMI of 35–39.9 kg·m^−2^. Upon identifying the participants, an intervention delivery schedule will be established. Before undergoing gastroscopy, participants will follow a 4-week IMT intervention protocol based on their assigned group. The timeline for enrollment, interventions, and assessments is outlined in detail in Table 1. All data will be collected according to the participant’s specific timeline, which includes the following time points: T1: 1 day before IMT, T2: immediately prior to anesthesia, T3: at the conclusion of the gastroscopy, T4: on the night of the gastroscopy, T5: 1 week after the gastroscopy, and T6: 4 weeks after the gastroscopy.

For participants assigned to the intervention group, a research assistant will measure their Pi(max) using the IMT device (POWER^®^breathe, Tianrui, Jiangsu). During the measurement process, patients will be seated and wear a nasal clip. They will exhale slowly and completely, followed by inhaling with maximum force and holding it for at least 1.5 s. The inspiratory pressure at this point will be recorded. This process will be repeated three times, and the average of the recorded inspiratory pressures will be considered as the Pi(max).

POWER^®^breathe follows a standard practice of conducting 30 inspiratory breaths twice a day (20). The intervention group will undergo IMT using a load equivalent to 30% of their Pi(max) during the first week. Starting the following week, the load will be increased by 10% each week for a total of three adjustments. On the other hand, participants in the control group will not receive any load during the 4-week IMT. It is important to note that participants will not be informed about their assignment to either the intervention or control group.

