### Blinding

The independent research assistant will have the responsibility of explaining the procedure and details of IMT and measuring the Pi(max) for all participants. The research assistant will conduct remote instruction and real-time monitoring of the participants through video software, making them unblinded to the process. However, both the participants and the research assistant will be explicitly instructed not to disclose any details to other researchers involved in the study.

On the other hand, the anesthesiologist, the endoscopist, data collectors, laboratory technicians, and biostatistician will be blinded to the intervention protocols and group allocation to ensure unbiased evaluation.

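### Reminders for the self-rated PSQI come from an assistant who knows the allocation, on no fixed schedule, so blinding of the follow-up sleep outcome is not assured

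*Protocol article*

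**What the plan says.** The Study design section carries the blinding label: "This study is a single-center, double-blinded RCT". The Blinding section describes a research assistant who instructs and watches participants by video, "making them unblinded to the process". It then says that, besides the anesthesiologist and the endoscopist, "data collectors, laboratory technicians, and biostatistician will be blinded to the intervention protocols and group allocation to ensure unbiased evaluation".

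The section on data collection, handling and monitoring turns to loss to follow-up. There, "a research assistant who knows the group assignment will reach out to patients from time to time", and the next sentence limits the task: "Their purpose is to remind patients to fill out the PSQI sheets".

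The PSQI is listed under Secondary outcomes. It is completed by the patient at T1, T2, T4, T5 and T6, and the note under Table 3 has the forms e-mailed to a designated anesthesiologist. The Statistical analysis section fills missing data by LOCF.

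For masking of participants, the Intervention section states that "participants will not be informed about their assignment to either the intervention or control group". The same section says that "participants in the control group will not receive any load during the 4-week IMT", while in the intervention group "the load will be increased by 10% each week for a total of three adjustments", starting from 30% of Pi(max).

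**The concern.** For a questionnaire about one's own sleep, the patient is the assessor. Its protection from bias therefore rests on two things: the patient not recognising the arm, and both arms being handled alike while forms are sought. The article blinds those who collect data, yet gives one step of obtaining PSQI data to a person who knows the allocation, at times that are not fixed.

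If that contact differs by arm, even unintentionally, two results follow. Forms may come back at different rates, and patients who are contacted more, or differently, may answer differently. A difference in sleep quality could then reflect contact or expectation rather than training. The discussion of study strengths presents sleep quality as something the trial will explore, so the outcome should be interpretable.

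**Working it through.** The plan gives no figure on this point, so the check sets its statements side by side.

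1. **Who reminds.** The data-collection section says outright that the person knows the assignment. This is a statement in the text, not a gap that a fuller document would fill. A full protocol could add a schedule or script, but the statement would still stand.

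2. **What restrains the contact.** The stated purpose is a reminder only. The non-disclosure instruction in the Blinding section forbids the assistant and participants from passing details to other researchers. It does not address what the assistant may convey to patients.

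3. **Which forms are exposed.** T1 is the day before training starts, so neither training nor felt load can have acted. T2 is immediately before anesthesia, when the patient is already with staff. T4 (night of the gastroscopy), T5 (1 week) and T6 (4 weeks) are completed afterwards, when loss to follow-up is the stated worry. The main exposure is therefore three of the five forms.

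4. **How unequal return enters the analysis.** Let m_I and m_C be the proportions of T6 forms not returned in the intervention and control arms. Suppose training has no effect on sleep and both arms have the same true mean μ at T6. Suppose also that, among patients without a T6 form, the mean change since the last returned form is δ in both arms.
   - LOCF mean in an arm = μ − m·δ
   - Intervention minus control = (μ − m_I·δ) − (μ − m_C·δ) = (m_C − m_I)·δ

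   This is zero when return is equal and non-zero when it is not (unless δ = 0).

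   As an illustration only, take the plan's 10% dropout as the overall non-return rate. That is an assumption, because the 10% was set for the sample size. Missing forms = 0.10 × 232 = 23.2. Split evenly, the spurious difference is 0. If all fell in one arm of 116, the difference in non-return would be 23.2 / 116 = 0.20. The artefact therefore lies between −0.20·δ and +0.20·δ, and these limits are extremes, not expectations. The article gives neither δ nor return by arm, and this covers only the return of forms, not a change in their content.

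5. **Masking of participants.** The one stated measure is that they are not told their group. One arm trains with no load for 4 weeks. The other starts at 30% of Pi(max) and has three increases. The list of blinded roles in the Blinding section does not name participants.

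6. **What is not touched.** The primary outcome is SpO2 below 90% during gastroscopy, with the anesthesiologist, endoscopist and data collectors stated to be blinded. The sample size (105 per group, 232 in total with dropout) is built on hypoxemia at 40% and 20% and does not depend on the PSQI.

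**The case against.** The article does not contradict itself. It declares the assistant unblinded and separates that role from those who record outcomes. The assistant is said only to remind. The form has largely fixed responses, is completed by the patient, and goes to an anesthesiologist, a role listed as blinded. Nothing says that one arm is contacted more than the other. All of this stands, and it limits the point to a route for bias rather than evidence of bias.

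Several stronger readings are tempting, but the documents do not support them:

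- A reader might infer that the person sending reminders also coached the patient for 4 weeks. The data-collection section speaks of a research assistant, the Blinding section of the independent research assistant, and neither says they are the same person.
- A reader might count all five PSQI forms as exposed. T1 and T2 are poorly placed for that, as shown above.
- A reader might infer that controls know their arm because they feel no resistance. Both arms train, and the article does not say that participants are told loaded and unloaded regimens are being compared. Feeling no load is a cue, not knowledge of the arm.
- A reader might fault the plan for not testing whether blinding worked. In a condensed article that is an omission which a full protocol may fill, so it is not counted here.

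What the objection does not remove is the explicit choice of someone who knows the allocation for a task that does not require that knowledge.

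**Conclusion.** The point holds in limited form. The plan states, and could easily avoid, a route by which handling of a self-rated secondary outcome may differ by arm. It mainly concerns the PSQI at T4, T5 and T6. LOCF would carry any imbalance in return into the comparison, and separate masking measures do not fully protect the content of the answers.

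The size and direction of any bias cannot be derived from the article. They depend on whether contact actually differs by arm and on how sleep scores change over follow-up, and neither is given. The article does not support the conclusion that blinding has failed or that the double-blind label is false for the trial as a whole. The primary comparison of hypoxemia is little affected. Changing the reminder arrangement is worthwhile because it removes the route at almost no cost.

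**What to change.** Replace the sentence on reminders in the data-collection section with automated messages that use one script and one fixed schedule in both arms. If a person must do it, use someone who does not know the allocation and records no other outcome. The blinded data collectors are not a good choice, because direct contact with patients could reveal the arm to those whose blinding protects the other outcomes.

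State that the PSQI will be interpreted as a self-reported outcome whose blinding is not assured, since participants are masked only by not being told their group while controls train without load. If patients are asked which arm they think they were in, ask after the T6 PSQI. Asking at T2 would draw attention to allocation just before the three forms that need protection.

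The cost is a small effort to set up the messages. The interventions, the primary outcome and the total of 232 stay as they are.
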